### **Recruitment of study participants**

Door-to-door visits will be done to identify families with the target children. The children will then be screened by a clinical officer. The consent form and procedures of the intervention will be explained to the parents of the eligible children and a thumb print or written informed consent obtained from the interested parents. A follow up will be done within 2 days to start the intervention.

### **Pilot study**

A Pilot study will be conducted (in Kiangombe slums, adjacent to Kiandutu slums and with similar socio-economic and demographic characteristics) on 10 % of the targeted sample size for each study group to optimize the study procedures, pre-test instruments and to provide information on other factors so as to aid in the planning of the main study.

### **Validity and reliability**

Questionnaires will be pre-tested in the pilot study to ascertain their reliability and validity. The Socio-demographic Questionnaire, FFQ and CEBQ used in this study have been validated (KDHS, 2008-09, Gibson & Ferguson, 2008, Wardle *et al.*, 2007).

### **Anthropometric measurements**

Weight will be measured on a pediatric balance-beam scale to the nearest 0.1 kg while length/height to the nearest 0.1 cm taken when nude. Recumbent length will be taken for children less than two years or those whose length is shorter than 87cm and height for those whose length is greater than 87 cm. Age as per birth date (Child Health Cards) will be taken. When such evidence misses, age will be estimated using the parent's estimates or local event calendars. Oedema will be confirmed if a shallow print remains on both feet, after applying thumb pressure for 30 seconds to the two feet simultaneously. ENA for SMART software will be used to standardize anthropometric measurements.

### **Data analyses**

The field data will be cleaned and coded and analyzed using SPSS software. Socio-economic (SE) status data will be reduced by using principal components analyses to an index using STATA. ENA for SMART will be used to analyse anthropometric data. The indices used to determine nutritional status will be; WA, HA and WH. Nutritional status will be judged by the WHO standards. Child feeding practices will be assessed using the indicators as per WHO (2001b) and WHO (2007) IYCF guidelines. Child feeding index, breastfeeding and complementary feeding (initiation, meal frequency and dietary diversity as a proxy for quality) will be determined. Nutrient intakes will be analyzed using Nutri-survey. Relative risk and odds ratio will be used to show the association between morbidity patterns and zinc status. Pearson product moment correlation and chi-square will be used to determine the relationship between non-categorical variables (feeding practices and nutrition status, SE status) and categorical variables (sex, age, type of illness and maternal characteristics) with zinc status respectively.

The relationships between the categorical variables will be analyzed to assess inter-group differences in dietary practices, nutrition status, morbidity patterns and serum and hair zn status at baseline, monthly and end of the study using chi-square and t-test, ANOVA and ANCOVA. Simple linear regression will be used to determine the contribution of sprinkles/CSB, dietary practices and SE status to nutrition status, morbidity patterns and

serum zn levels. Multiple regression analysis will be used to determine the extent to which sprinkles/fortification, dietary practices and predict nutrition status, morbidity patterns and serum zn levels and logistical regression used to analyze for confounding variables. Content analysis will be used for qualitative data from FGDs by summarizing the information into emerging themes. Bioequivalence of sprinkles to CSB will be drawn if the percentages of children with serum zn  $<9.9 \mu\text{mol/L}$  is within  $\pm 20$  rule (excluding CRP levels  $>10 \text{ mg/l}$ ), the basis to accept or reject the null hypothesis. Significance will be determined at 95% confidence interval, P-value of 0.05.

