### **Description of the intervention**

CSB (80% corn and 20% soy) and sprinkles meeting 100% RDA of zinc will be sourced from suppliers. For a period of six months, sprinkles (1g) will be added to corn-soy porridge once daily and CSB porridges made from 100g flour will be given daily (Figure 1). The micronutrient composition of the different study groups is shown in Table 1. The food supplements will be prepared in feeding centres. De-worming will be done at the start of the intervention using mebendazole (500 mg). Demonstrations on porridge preparation and use of sprinkle and nutrition education focused on the importance of nutritious diet will be given to the primary caregivers on group basis at baseline.

Table 1: Micronutrient composition of sprinkles and CSB

|                  | Expt Gp 1:
Sprinkles (per 1
g sachet) | Expt Gp 2:
Sprinkles* (per 1
g sachet) | Expt Gp 3:
Sprinkles* (per 1
g sachet) | Comparator Gp
4: CSB ( 100g
dry wt.) |
|------------------|------------------------------------------------------|-------------------------------------------------------|-------------------------------------------------------|-----------------------------------------------------|
| Vit A (IU)       | -                                                    | 1250                                                  | 1250                                                  | 1300                                                |
| Vit E (mg)       | -                                                    | 6.0                                                   | 6.0                                                   | -                                                   |
| Vit C (mg)       | -                                                    | 30                                                    | 30                                                    | 30                                                  |
| Thiamine (mg)    | -                                                    | 0.5                                                   | 0.5                                                   | 0.1                                                 |
| Riboflavin (mg)  | -                                                    | 0.5                                                   | 0.5                                                   | 0.4                                                 |

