### **Data collection tools and procedures**

Baseline data on children's past and present illnesses will be obtained by interviewing the primary caregivers and from confirmation from health cards. A semi-structured questionnaire designed to elicit information on the household socio-economic, demographic structure, parental education and employment, material possessions and type of housing materials. A 24-hour recall designed for measuring nutrient intakes inclusive of zinc will be used and a Food Frequency Questionnaire (FFQ) will be administered to cover the most commonly consumed complementary foods based on a 7-day recall. Appetite will be assessed monthly using the Children's Eating Behaviour Questionnaire (CEBQ),

Serum zn, albumin and CRP will be determined at baseline and post-intervention. Monthly anthropometric measurements and dietary intake will be conducted monthly for the 6-month period. Interviewers will visit the childrens' homes bi-weekly to inquire about symptoms of illness (severity, frequency and duration) of diarrhoea, ARTI and other infections, and monitor the feeding practices.

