### 3.4.6 Sample size determination

Determination of sample size will be based on the primary objective and the formula by Liu

& Chow (1992). Where; 
$$n = \frac{(Z_{\alpha} + Z_{\beta})^2 \sigma^2}{(\delta - \varepsilon)^2} = \frac{(1.64 + 1.28)^2 0.71^2}{(0.2 - 1.0)^2} = 67$$

Where; n = No. of study subjects per group,  $\sigma$  = variance within the groups,  $\delta$  = expected outcome difference of the groups (20 % as per the bioequivalence rule),  $\varepsilon$  = the absolute values of proportion differences among the groups. The standard normal deviate at the required confidence interval (95 probability error).

The prevalence of zinc deficiency in Kenya is 50% (GOK & UNICEF, 2008). The estimated post-intervention prevalence of 20%, 10%, 20% and 50% for the reference, ZN, ZN in MMN and MMN without ZN groups respectively. To show equivalence within 20% rule with 80% power and 5% significance, a sample size of 67 per group was obtained and allowing 20% attrition, a sample size of 80 per group is obtained.

Where; n = The desired sample size, z = The standard normal deviate at the required confidence interval (95 probability error equal to 1.96), p = The proportion of occurrence of the phenomenon (0.5) since prevalence is 50%, q = The proportion of non-occurrence is (1-P) = 0.5, d = level of statistical significance (0.05 for 95% level of significance).

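### Illness frequency and duration are collected for six months, but the named illness analyses use no child-time observed: six-month yes/no measures would lose information, and none allows for unequal observation time

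*Protocol*

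**What the plan says.** **Data collected.** Under Data collection tools and procedures, interviewers will "visit the childrens' homes bi-weekly to inquire about symptoms of illness (severity, frequency and duration) of diarrhoea, ARTI and other infections". Description of the intervention sets the follow-up: "For a period of six months, sprinkles (1g) will be added to corn-soy porridge once daily". The raw material is therefore recurrent episodes and days ill, gathered repeatedly on each child.

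**Analysis named.** Data analyses gives three routes for illness:
- Against zinc status: "Relative risk and odds ratio will be used to show the association between morbidity patterns and zinc status". Chi-square is also named for type of illness and zinc status.
- Between groups: inter-group differences, morbidity included, are assessed "at baseline, monthly and end of the study using chi-square and t-test, ANOVA and ANCOVA".
- Regression: "Simple linear regression will be used to determine the contribution of sprinkles/CSB, dietary practices and SE status to nutrition status, morbidity patterns" and serum zinc. Multiple regression is named for the same outcomes, and logistic regression for confounding.

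**Not named.** There is no incidence rate, proportion of days ill, count model, child-time denominator or method for repeated episodes. The morbidity variable is not defined.

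**Attrition.** Section 3.4.6 raises 67 per group to 80, "allowing 20% attrition". Nothing says how a child with incomplete follow-up enters the illness analysis.

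**The concern.** Relative risk, odds ratio and chi-square need a yes/no or categorical outcome. A child with one short cold and a child with five long bouts of diarrhoea become the same observation once both are classed as ill. If the window is six months and illness is frequent, nearly every child is classed as ill and the measure has little left to compare. Relative risk and odds ratio then also give very different impressions of one effect.

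Observation time is a separate matter. A child seen for two months has less opportunity to report episodes than one seen for six. Without a time denominator, short follow-up or missed visits can pass for good health. If observation time differs between groups or zinc-status classes, part of an apparent illness difference may be only a difference in how long children were watched.

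**Working it through.** The Protocol states no illness rate, illness effect size or illness power, so there is no figure to reproduce. What follows is illustration.

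**Inputs from the Protocol:** six months of follow-up; 80 enrolled per group; 20% expected attrition; significance level 0.05 (taken as two-sided).

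**Assumed, not in the Protocol:** 2, 4 or 8 episodes per child-year; rate ratio 0.80 (step 1) or 0.70 (step 2); gamma variation between children with k = 2; dropout times uniform over follow-up; children independent.

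**Step 1. Saturation, by window.** With Poisson episodes, the chance of any illness is 1 − exp(−rate × T). For 4 per year over half a year: 1 − exp(−2) = 0.865. With the rate cut to 0.80 of that: 1 − exp(−1.6) = 0.798. The relative risk is 0.798/0.865 = 0.92 and the odds ratio is (0.798/0.202)/(0.865/0.135) = 0.62.

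| Rate per year | Window | Any illness | RR | OR |
|---|---|---|---|---|
| 2 | 6 months | 63% | 0.87 | 0.71 |
| 4 | 6 months | 86% | 0.92 | 0.62 |
| 8 | 6 months | 98% | 0.98 | 0.44 |
| 2 | 1 month | 15% | 0.81 | 0.79 |
| 4 | 1 month | 28% | 0.83 | 0.77 |
| 8 | 1 month | 49% | 0.85 | 0.74 |

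The true rate ratio is 0.80 in every row. Over six months the two measures move apart as illness becomes commoner. Over one month both stay fairly near 0.80.

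**Step 2. Power.** Simulated trials with 80 per arm, rate ratio 0.70, 20% attrition in both arms and k = 2; ranges span repeated runs.

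| Rate per year | Any illness in 6 months | t-test on counts | Rate |
|---|---|---|---|
| 4 | 22–24% | 48–51% | 52–55% |
| 8 | 19% | 63% | 67–68% |

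At 2 per year, any illness has 23% and the rate 38%. With k from 1 to 4 at 4 per year, any illness has about 17–30% and the rate about 40–65%. When illness is rare the gain shrinks: at 0.1 episodes per month, Poisson counts and 67 per group give 25% against 31%.

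**Step 3. Unequal observation time, no true effect.** Suppose dropouts stay in the denominator and leave, on average, halfway. Attrition of 10% in one group and 30% in the other gives a mean-count ratio of

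(0.7 + 0.3 × 0.5) / (0.9 + 0.1 × 0.5) = 0.85/0.95 = 0.89.

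For any illness at 0.5 episodes per month, completers show 95.0% and dropouts 68.3%, so the ratio is

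(0.7 × 0.950 + 0.3 × 0.683) / (0.9 × 0.950 + 0.1 × 0.683) = 0.870/0.923 = 0.94.

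In simulation at 2 to 8 episodes per year, false positives at the nominal 5% level are about 8–12% for any illness and for the t-test on counts, against about 5% for the rate. With equal attrition the two groups lose the same share, and the bias between them largely cancels.

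**The case against.** **Several named methods do not discard the counts.** The t-test, ANOVA, ANCOVA and linear regression accept episode counts or days ill, and step 2 shows a t-test on counts within about 4 points of the rate. A reader might infer that the illness comparisons between products lose most of their power. The Protocol does not support that: the loss is confined to the yes/no analyses. This part of the objection stands.

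**The six-month ever-ill window is not stated.** The group comparisons are also monthly, where saturation is slight. This stands too. The relative-risk and odds-ratio sentence gives no window, however, so nothing rules out the damaging one.

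**Dropouts need not look healthier.** A reader might take it that children who leave early will count as healthy. The Protocol does not say that they are kept as if fully observed. A completers-only comparison of counts holds 5% false positives when dropout is uninformative; its risk is selection. A monthly comparison confines the effect to the month of leaving. For zinc status the route is narrower still: serum zinc is measured only at baseline and after the intervention, so a child lost in month 2 cannot enter an association with endline zinc. The bias would need baseline zinc set against follow-up illness, or missed visits among children who stay.

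**Definitions may sit in an SAP.** Episode rules and handling of partial follow-up often do, and their absence here is not itself the point. But the Protocol names its effect measures and tests, and those choices can be judged as written.

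**Conclusion.** The point holds in a limited form. The yes/no measures named for illness and zinc status would discard much of the collected information if taken over six months when illness is common: about 19–24% power against 52–68% for a rate, at an assumed 4 to 8 episodes per child-year. Analyses of counts largely avoid that loss, and monthly windows largely avoid saturation. No named method, as described, protects against unequal observation time. That matters only if partially observed children are kept unadjusted and observation time differs by group or zinc status; an assumed 10% against 30% attrition then gives a false count ratio of about 0.89 and 8–12% false positives.

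Illness rates, effect size, dispersion and the attrition split are all assumptions; the Protocol gives only one overall 20%. The power figures treat children as independent although villages are randomized, so they compare methods and do not forecast the trial's power. Sample size and the bioequivalence decision rest on zinc deficiency, so the primary conclusion is not affected. The change is worth making as an improvement to a secondary analysis.

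**What to change.** In Data analyses:
- Define the illness outcomes as episodes, and days ill, per child-time actually observed. A missed visit is unobserved time, not illness-free time.
- As the main illness analysis, compare study groups, and zinc-status classes, by rate ratios from a count model that allows overdispersion (negative binomial, for example), with log observed child-time as offset and village accounted for.
- If relative risks are kept, state a short window for them, such as one month.

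**Cost:** revised analysis wording, an episode definition, a little more analysis work, and a mark for missed visits on the visit form. No extra visits, staff or samples are needed.

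### Outside the ±20 rule on serum zinc, growth, illness and diet are tested between four arms monthly and at the end, each at P 0.05 with the test left open, which allows unsupported secondary claims of a product effect

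*Protocol*

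**What the plan says.** The Data analyses section of the protocol sets out the between-arm testing itself. It will compare the arms on diet, nutrition status, illness and "serum and hair zn status at baseline, monthly and end of the study using chi-square and t-test, ANOVA and ANCOVA". It then relates nutrition status, morbidity and serum zinc to sprinkles/CSB, diet and socio-economic status by simple regression and again by multiple regression. One rule covers all of this: "Significance will be determined at 95% confidence interval, P-value of 0.05".

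The size of the family follows from the rest of the text:

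- Growth: "The indices used to determine nutritional status will be; WA, HA and WH".
- Illness, from bi-weekly home visits (Data collection tools and procedures): "symptoms of illness (severity, frequency and duration) of diarrhoea, ARTI and other infections".
- Timing, same section: "Monthly anthropometric measurements and dietary intake will be conducted monthly for the 6-month period", but "Serum zn, albumin and CRP will be determined at baseline and post-intervention".
- Arms: four, three villages each (Randomization).

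The Data analyses section also contains one decision rule. Bioequivalence of sprinkles to CSB is judged on the percentage of children with serum zinc below 9.9 µmol/L, within ±20, leaving out children with CRP above 10 mg/l. That rule is the stated basis for accepting or rejecting the null hypothesis.

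**The concern.** Apart from the ±20 rule, no outcome, month or pair of arms is named in advance as the one to be read. For a continuous outcome such as WH, the same comparison could be made by t-test, ANOVA or ANCOVA, and nothing says which. Each result is held to P 0.05, and none is called secondary or exploratory.

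Followed as written, a single favourable month, index or pair of arms could be reported as a significant effect of a product on growth or illness. Such a claim would be a natural one here: the Target population section gives the possible benefit of zinc in children with growth failure as the reason for choosing moderately malnourished children. What is at stake is the credibility of the secondary claims.

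**Working it through.** The protocol states no family-wise error figure, so there is nothing to reproduce. The check asks how often at least one test falls below 0.05 when all four arms are truly equal.

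**Inputs from the protocol.** Per-test level 0.05; four arms; three growth indices (WA, HA, WH); three illness outcomes (diarrhoea, ARTI, other infections); six monthly rounds.

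**Assumptions, not in the protocol.** One overall four-arm test (3 df) per outcome and month unless stated; correlations between outcomes and between months as given below; each test has a true size of 5%, so clustering by village is ignored. Baseline tests and diet are not counted.

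**Formula for independent tests.** Chance of at least one false positive among k tests = 1 − 0.95^k. For k = 6 this is 1 − 0.735 = 0.265. Correlated tests were simulated with 200,000 replicates.

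| Family | Assumed correlation | Chance of at least one P < 0.05 |
|---|---|---|
| One outcome, one time, all six pairs of arms | – | 20% |
| One outcome, one time, three sprinkles arms v CSB | – | 13% |
| Six outcomes, one time | 0 / 0.5 / 0.8 | 26% / 21% / 15% |
| One outcome, six months | 0.5 / 0.8 / 0.9 | 21% / 15% / 11% |
| Six outcomes × six months | 0.5 between outcomes, 0.8 between months | 47% to 50% |

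In the last row, 47% takes the correlation between different outcomes as 0.5 whatever the months; 50% lets it fall to 0.5 × 0.8 = 0.4 when the months differ.

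**A smaller family.** WA, HA and WH alone over six months give 34% with the same correlations, and 19% with 0.7 between indices and 0.95 between months.

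**A different count.** Take diet, nutrition status and morbidity as one outcome each over six months, plus serum and hair zinc at the end only: 3 × 6 + 2 = 20 tests. Independence gives 1 − 0.95^20 = 0.64. Correlations of 0.5 to 0.9 between months and 0.3 to 0.5 between outcomes give 0.54 down to 0.31.

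Every row is more than twice the nominal 5%. The second row also shows that three unadjusted comparisons with CSB on one outcome already exceed it, so dropping the monthly tests does not by itself restore 5%.

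**The case against.** The strongest reply is that the SAP is not shown, and that handling of multiplicity for supportive outcomes commonly sits there. Its absence from a protocol is no finding. That is right as far as it goes. But this protocol does more than stay silent: it fixes the comparisons, the months and the threshold for all of them. The point concerns that stated rule.

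Several stronger readings are tempting, and the document does not support them:

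- *That the protocol has no hierarchy at all.* It has one deciding rule, the ±20 comparison on low serum zinc, and the sample size is tied to the primary objective. A chance P < 0.05 on WH or diarrhoea cannot alter the decision on the null hypothesis.
- *That zinc is tested every month.* The Data analyses wording could be read so, but serum zinc is measured only at baseline and post-intervention, and the ethics section says blood is drawn twice. The wording needs reconciling; there are no monthly serum zinc tests to count.
- *That four interchangeable tests are applied to each outcome.* Chi-square serves categorical data. The open choice is among t-test, ANOVA and ANCOVA. The regressions also address diet and socio-economic status, so they are not mere repeats of the arm comparison.
- *That baseline tests add false product effects.* They precede treatment and cannot show one. They are merely uninformative between randomised arms.
- *That a chance significant finding is likely.* The main figures run from 11% to about one half. Higher ones (60% to 93% for the 20-outcome count with unadjusted comparisons against CSB) depend on test counts and correlations that the protocol does not give.

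It is also fair to say that these percentages do not describe the trial exactly, because three villages per arm are ignored. If children are analysed as independent and villages differ, each test would exceed 5%, so the omission does not flatter the plan's critics. Finally, reporting a chance result as an effect is a possible use of the plan, not something it announces. That limits the weight of the point.

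**Conclusion.** The concern holds for the secondary outcomes only. The protocol applies P 0.05 to each between-arm test of growth, illness and diet, monthly and at the end, leaves the test open for continuous outcomes, and does not separate these results from confirmatory ones. With no true product difference, at least one nominally significant growth or illness result would arise with a chance of about 11% to 26% for six tests, and about 47% to 50% for six outcomes by six months. The sizes rest on assumed correlations, on one overall test per outcome and month, and on ignoring clustering; the direction does not depend on the particular values tried. The bioequivalence verdict is unaffected. The change is worth making because it is cheap and prevents unsupported claims, but it does not put the main conclusion in doubt.

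**What to change.** Amend the Data analyses section as follows.

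1. State that the ±20 comparison on low serum zinc is the only confirmatory analysis. Since there are three sprinkles arms, the sentence should also say which of them it compares with CSB.
2. Call all other between-arm comparisons and regressions secondary or exploratory, and report them as estimates with 95% intervals and without significance claims.
3. Replace the month-by-month tests with one end-of-study comparison of each sprinkles arm with CSB per outcome: baseline-adjusted ANCOVA for WA, HA and WH, and illness over the six months for morbidity. The analysis must allow for allocation by village; otherwise its intervals would be too narrow if villages differ. The monthly data can still be described.
4. Describe baseline by arm without significance tests.
5. Reconcile the monthly wording with the two serum zinc time points given in Data collection tools and procedures and in the ethics section.

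A formal multiplicity procedure for secondary outcomes, such as Holm, would be needed only if a confirmatory growth or illness claim were wanted; that is the sponsor's choice. The cost is protocol wording and fewer secondary results that can be called significant. No extra children or data are needed.

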### **Randomization**

The sampling frame will consist of the 12 villages in Kiandutu slum. Three villages will be randomly allocated to each of the 4 study groups. Villages rather than study subjects will be randomized to avoid cross-contamination of information due of the close proximity of the study subjects. Computer generated randomization will be done by a statistician.

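### Monthly between-arm tests at 0.05, with no repeated-measures method and no deciding month, raise the false-positive chance for each supporting outcome to about 9% to 26%

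*Protocol*

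**What the plan says.** Under Data collection tools and procedures, the protocol states: "Monthly anthropometric measurements and dietary intake will be conducted monthly for the 6-month period". Appetite is also assessed monthly by questionnaire. For morbidity, "Interviewers will visit the childrens' homes bi-weekly to inquire about symptoms of illness".

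Under Data analyses, the arms are to be compared "to assess inter-group differences in dietary practices, nutrition status, morbidity patterns and serum and hair zn status", and this is to be done "at baseline, monthly and end of the study using chi-square and t-test, ANOVA and ANCOVA". The threshold is general: "Significance will be determined at 95% confidence interval, P-value of 0.05". The section adds simple, multiple and logistic regression. It names no repeated-measures or mixed model, no principal month and no adjustment for testing at several months. ANCOVA is listed without its covariate.

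Serum zinc is handled differently. "Serum zn, albumin and CRP will be determined at baseline and post-intervention", and the trial's main conclusion is one rule: "Bioequivalence of sprinkles to CSB will be drawn if the percentages of children with serum zn" below a cut-off lies within a 20% margin.

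**The concern.** The stated tests, their timing and their threshold together give about six post-baseline answers for each supporting outcome, each with its own 5% error, and no rule for which one counts. An arm could be reported as better or worse on growth, diet or illness because a single month fell below 0.05 by chance.

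This is separate from the village randomisation. It would arise even if children had been randomised individually, because it comes from looking repeatedly at the same children. It is also more than a detail left for later: the protocol fixes the method, and an analysis plan that followed it would inherit the problem.

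**Working it through.** **Inputs from the protocol**
- Four arms (Study design; Randomization: "Three villages will be randomly allocated to each of the 4 study groups").
- Six monthly rounds after baseline (Data collection tools and procedures). The end-of-study comparison is taken to be month 6.
- 0.05 for each test (Data analyses), with no adjustment stated.

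**Assumptions**
- One test per month per outcome: a four-arm ANOVA on a continuous measure.
- No true arm effect and no village effect.
- Within-child correlation between months (rho): not given in the protocol, so a range is used.

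The protocol gives no error rate over months to reproduce. The reference figure is its 5% per test.

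**Step 1. Upper end: months independent.**
1 − (1 − 0.05)^6 = 1 − 0.95^6 = 1 − 0.735 = 0.265, or 26.5%. Ratio to 5%: 26.5 / 5 = 5.3.

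**Step 2. Months correlated within child.** There is no simple closed form, so 100,000 null trials were simulated per setting, with normal arm means and known variance. The quantity counted is the share of trials in which any of the six monthly ANOVAs is significant.

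| rho | Equal correlation between all months | Ratio to 5% | Correlation decaying as rho^(months apart) |
|---|---|---|---|
| 0.3 | 24.2% | 4.8 | 25.6% |
| 0.5 | 21.3% | 4.3 | 24.1% |
| 0.7 | 17.2% | 3.4 | 20.4% |
| 0.8 | 14.4% | 2.9 | 17.6% |
| 0.9 | 11.3% | 2.3 | 13.8% |
| 0.95 | 9.2% | 1.8 | 11.1% |

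A single two-arm t-test each month gives nearly the same: 20.9% at rho 0.5, 13.8% at 0.8 and 10.7% at 0.9 (equal correlation).

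**Step 3. After the change.** One prespecified test per outcome has a nominal 5% over the months, provided village clustering is also handled. Keeping all six tests under a Bonferroni correction would require 0.05 / 6 = 0.0083 at each.

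**Step 4. Which single contrast to name.** Take 67 children per arm, two arms compared, a 0.4 SD difference at month 6, adjustment for baseline and no village effect. Suppose the effect builds linearly from zero. The average effect over months 1 to 6 is then 0.4 × (1+2+3+4+5+6)/(6 × 6) = 0.4 × 21/36 = 0.233 SD.

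| Correlation | Power, month-6 difference | Power, six-month average |
|---|---|---|
| Equal, 0.5 | 76% | 64% |
| Equal, 0.7 | 90% | 75% |
| Decaying, 0.8 per month | 66% | 53% |

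For an effect that builds up, the month-6 contrast has more power. For an effect constant from month 1, the average does, because averaging six values reduces the noise while the effect stays at 0.4 SD. Neither is better in general, so the choice has to be made per outcome and in advance.

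**The case against.** **The main conclusion is not touched.** This stands. Serum zinc is measured twice and bioequivalence is decided by one rule. The Data analyses sentence lists serum and hair zinc among the monthly comparisons, but serum zinc has no monthly values to test. The point is confined to supporting outcomes.

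**Error control for supporting outcomes is often left to an analysis plan.** True of omissions. Here the protocol states the tests, the months and the threshold, and it is that stated method that is unsuitable.

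**ANCOVA is listed, and ANOVA is not said to be one-way.** A reader might infer that the plan never links a child's values. That is too strong: ANCOVA with baseline as covariate would link baseline to one later value. It would still leave six separate tests. A repeated-measures ANOVA is not excluded, but nothing names one, and the wording ties the tests to each month.

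**The size depends on an unstated correlation.** This stands. A reader might settle on a fixed multiplier such as three to four times; that needs an equal correlation of about 0.6 to 0.8, and growth and diet need not share the same value.

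**Larger error rates could be claimed.** A reader might suppose that all six arm pairs are t-tested every month, or that monthly records are stacked as if from different children. Either would give higher rates, but the protocol states neither, and much of the first would come from having four arms.

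**Separate monthly tests need not lose power.** This stands. A reader might infer that a real growth effect is more likely to be missed under the plan. Step 4 shows that a baseline-adjusted month-6 comparison can have more power than the six-month average, so no general loss is claimed.

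**Conclusion.** The point holds for the supporting outcomes that are measured repeatedly and compared monthly: nutrition status, dietary practices and morbidity. It extends to appetite if that is compared between arms in the same way, since the comparison sentence does not list it. For a continuous outcome with one four-arm test in each of six months, the chance of at least one false arm difference is about 9% to 26%, or about two to five times 5%. This rests on an assumed within-child correlation from 0.95 down to 0, and on each monthly test holding its own 5% level. Child-level tests in a trial of 12 randomised villages may not hold that level; that is a separate matter. The figures are for continuous measures; the illness data were not simulated. The serum zinc bioequivalence conclusion is unaffected. The change is worth making but does not bear on the primary result.

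**What to change.** In Data analyses:

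- Replace the separate monthly tests of anthropometric indices, dietary intake and appetite with one longitudinal model per outcome. The response is all post-baseline months; the terms are arm, month and arm-by-month, with the child's baseline value as covariate and random effects for child and village.
- Name in advance one contrast per outcome as its test. The month-6 difference suits effects that build up over time; the six-month average suits effects that are constant.
- Report the other months as estimates with confidence intervals, without significance statements.
- For the bi-weekly illness data, use one summary per child (for example, days ill over days observed), or a count model with child and village random effects, so that visits are not counted as independent.
- If ANCOVA is kept anywhere, name its covariate.

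The cost is wording and a mixed-model procedure in SPSS or STATA, both already named. No new children, visits or measurements are needed. The small downside is fewer month-by-month significance statements.
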